### Study design

This study is a community-based, cluster-randomised controlled evaluation with two parallel groups: APCNF (‘intervention’) versus conventional practices (‘control’). A total of 80 clusters will be randomly allocated 1:1 to intervention or control. The study will run for 48 months, including evaluation development and setup; baseline, midline, and endline assessments; intervention implementation (24 months); laboratory measurements of biomarkers; and statistical analysis. The main study assessments will be conducted during monsoon cultivation (July-December) with a brief survey also conducted after the monsoon harvest (January-February). The same random subset of households enroled at baseline from each cluster will be followed at 12 and 24 months post-baseline assessment.

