### Selection of clusters and random allocation procedures

A list of clusters in which APCNF has not yet been implemented will be provided by RySS and the evaluation team will randomly select clusters for inclusion in the BLOOM study from this list using simple random sampling. By purposefully enrolling clusters where RySS has never before worked, we will minimise what has been described elsewhere as the ‘[NGO] reputation effect’ [83]. In a previous randomised controlled trial in India, this reputation effect–meaning prior engagement with target communities–was shown to bias intervention effectiveness by at least 30% [83].

The study will be explained to elected representatives in the village as well as other stakeholders (e.g., community health workers and Anganwadi [government childcare centre] workers) and their permission sought. Given the narrow agricultural season window, clusters will be randomised to intervention or control after recruitment and enrolment, and the list shared in confidence with RySS so that they can begin planning implementation activities for intervention clusters. No implementation activities will begin, and data collectors and participants will not be informed of the randomisation status, until the baseline assessment is complete. Randomisation will be stratified by original district (Kurnool and Vishakhapatnam).

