
### Additional assessments

Demographic and socio-economic data will be collected at baseline for all participants using questions adapted from the 5^th^ round of the Indian National Family Health Survey (NFHS-5) [5]. Specific variables to be assessed include age, sex, marital status, educational attainment, occupation, caste, cooking fuel, source of drinking water, toilet facility, household construction materials, and asset ownership including livestock. A household wealth index will be calculated from these variables using principal components analysis.

Information on cropping pattern, land cultivated, land irrigated, and land owned, in both Kharif (monsoon season) and Rabi (winter season), will be collected using questions adapted from the Indian Agriculture Census [103] and NSSO Situation Assessment Survey of Agricultural Households [102]. Farmer estimates will be used to estimate crop yields, quantity sold, where it was sold, and the sale value. This survey will also include questions on chemical input use, pesticide storage, and all expenses relating to crop production in the past 12 months (seeds, soil, fertilisers, manure, pesticides, diesel, electricity, human labour, animal labour, irrigation, minor repairs and maintenances, machinery hire, and lease rent for land). Detailed information will be collected from all adult participants on years working in agriculture; how many days per week and hours per day engaged in agricultural work; and which specific agricultural activities are undertaken. For those reporting activities relating to pesticides (e.g., mixing, loading, and/or application), additional information on chemicals used, application rate, method of mixing, method of application, use of personal protective measures and/or equipment, and personal hygiene practices will be collected. This survey will also query domestic use of pesticides for insect control. Questions are adapted from a survey on pesticide use in Thailand [93].

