### Power calculations

Power calculations were conducted using PASS 2019, v19.0.6 (NCSS, Kaysville, Utah, USA), accounting for the cluster-randomised design. Whilst hypotheses for the two primary outcomes (urinary pesticides and dietary diversity) were independent, in order to be conservative, a Bonferroni correction was applied (0.05/2, which is the number of primary outcomes) resulting in a two-sided alpha level of 0.025. It is expected that approximately 20% of the baseline sample will be loss-to-follow-up at 12 months. Two previous surveys in Andhra Pradesh by study team members had much lower loss to follow-up rates [2% from 2019 to 2020 in the SHEFS (Sustainable and Healthy Food Systems) nutrition survey (unpublished) and 10% for the mWellcare trial [104] but a higher rate was anticipated for the BLOOM study due to COVID-19.

Power for the primary outcomes is given in Table 5, which summarises the minimal detectable difference in mean levels associated with 80% power, a type I error rate alpha of 0.025, an intra-cluster correlation of 0.02, and 20% loss to follow-up. For ∑DAPs power calculations are shown for 150 per arm (a 15% subsample). Results in Table 5 confirm that the study is adequately power to detect a smaller difference than has been previously reported in the literature for these outcomes.

**Table 5 pone.0281677.t005:** Minimum detectable mean difference, with 80% power, alpha = 0.025, and intra-cluster correlation of 0.02.

	Standard Deviation for Mean Change in Outcome	Sample Size per Group	Minimum Detectable Mean Difference	Previous Study Estimate (95% Confidence Interval)
Change in mean ∑DAPs, adult men	111 μmol/l*	150	39.6 μmol/l (~55% of estimated baseline levels*)	-88% (not reported)^†^
Change in mean ∑DAPs, adult women	111 μmol/l*	150	39.6 μmol/l (~55% of estimated baseline levels*)	-88% (not reported)^†^
Change in mean ∑DAPs, children	17.3 nmol/l^‡^	150	6.17 nmol/l (~9.7% of estimated baseline levels^‡^)	-42.7% (-76.3–38.7)^‡^ -39.9% (-58.6, -12.6)^§^
Change in mean dietary diversity score, adult women	1.57^¶^	1000	0.29	0.36 (0.03–0.69)^¶^
Change in mean dietary diversity score, children	1.40^#^	1000	0.26	0.39 (0.13–0.64)^#^

* From an observational study of adult agricultural labourers in North Carolina [105].

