### Statistical analysis plan

The main analyses will be intent-to-treat, i.e., participants will be analysed as assigned, regardless of their fidelity to APCNF practices. Herein the analyses for primary outcomes are described. Analyses for secondary outcomes will be analogous. Separate models will be run for each of the primary outcomes. All primary outcomes are continuous. General estimating equation (GEE) models with robust standard errors will be used to account for within-participant correlations [111]. Models will account for clustering within villages. The models will take the form of:

$$Y_{i,t}=\beta_{0}+\beta_{1}Group+\beta_{2}Time+\beta_{3}Group*Time+\beta_{4}District+\varepsilon_{i,t}$$
(1)

where group is APCNF or control, time is baseline or 12 months, and district is Kurnool or Visakhapatnam (to account for randomisation stratification). β_3_ represents the difference in the change from baseline to 12 months in the APCNF group and the change from baseline to 12 months in the control group (e.g., difference in difference).

We will evaluate whether missing data are differential between groups using t-tests. We will assume missing data to be missing at random and conduct a complete-case analysis. Inverse probability weighting will be used to account for loss to follow-up. We will run adjusted models to address potential baseline imbalance across clusters and improve precision. Covariates will be selected based on p-values for differences across groups.

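### Covariates for the adjusted models are to be chosen by p-values between randomised arms, which selects on chance imbalance and gives up most of the precision sought

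*Protocol article*

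**What the plan says.** The Statistical analysis plan section of the protocol article first fixes the main model, Eq. 1, with terms for group, time, group by time and district. It defines them as follows: "where group is APCNF or control, time is baseline or 12 months, and district is Kurnool or Visakhapatnam (to account for randomisation stratification". The effect of interest is β3, which "represents the difference in the change from baseline to 12 months in the APCNF group" and the corresponding change in control.

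Two sentences at the end of the section then add a second set of models. The purpose is given as: "We will run adjusted models to address potential baseline imbalance across clusters and improve precision". The selection rule is: "Covariates will be selected based on p-values for differences across groups". Since group has just been defined as trial arm, these are p-values comparing APCNF with control. The preceding sentence shows that baseline differences are meant.

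On allocation, Study design states: "A total of 80 clusters will be randomly allocated 1:1 to intervention or control". The section on selection of clusters and allocation places randomisation after recruitment and enrolment, and keeps the result from participants and data collectors until baseline is finished. Additional assessments lists the demographic and socio-economic variables collected at baseline: "age, sex, marital status, educational attainment, occupation, caste, cooking fuel, source of drinking water, toilet facility, household construction materials, and asset ownership including livestock". A wealth index and land variables come on top of these.

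**The concern.** A covariate improves precision because it predicts the outcome, whether or not it is balanced between arms. A p-value comparing arms at baseline carries no information on prognosis. Under randomisation its null hypothesis is true by design, so a small value marks an unlucky draw. The rule therefore omits strong predictors that happen to be balanced and admits unrelated variables that happen to differ. This works against the precision aim given in the sentence just before it.

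The covariate set also cannot be known until the data by arm have been examined. Separate models are run for each primary outcome and the secondary analyses follow the same pattern, so the sets may differ from outcome to outcome. At stake are the usefulness and comparability of the adjusted estimates, not the main result.

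**Working it through.** The plan gives no figure on this point, so there is nothing to reproduce. The checks below show how the rule behaves. The threshold, the number of candidates and the prognostic strength are assumptions, because the article gives none of them.

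**1. Chance that a given covariate is picked.** Under randomisation, a valid baseline test at threshold α flags any covariate with probability α, however prognostic it is. This gives 5% at 0.05, 10% at 0.10 and 20% at 0.20.

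**2. Chance that something is picked.** For k independent candidates at 0.05 the chance is 1 − 0.95^k:
- k = 10: 1 − 0.599 = 0.40
- k = 15: 1 − 0.463 = 0.54
- k = 20: 1 − 0.358 = 0.64

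The quoted list alone holds 11 variables. These figures describe how often a data-driven set arises; they do not measure bias.

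**3. Precision.** The simulation used 3,000 runs of 80 villages with 25 people each, the plan's intra-cluster correlation of 0.02 (Power calculations), no true effect, and 10 candidate covariates. One of these correlated 0.5 with the follow-up outcome. The model was for the follow-up outcome, with village-robust standard errors. Baseline tests were done on village means at 0.05.

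| Adjustment | SD of effect | Mean SE | Type I error (nominal 0.05) |
|---|---|---|---|
| None | 0.0535 | 0.0538 | 0.044 |
| Prognostic covariate fixed in advance | 0.0463 | 0.0466 | 0.046 |
| Chosen by p < 0.05 | 0.0518 | 0.0535 | 0.039 |

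- Fixed in advance: (0.0535 − 0.0463)/0.0535 = 13% lower SD.
- Chosen by p-value: (0.0535 − 0.0518)/0.0535 = 3% lower SD.
- Share of the gain kept: 0.0017/0.0072 = 24%.
- The reported SE hardly moves under the rule: (0.0538 − 0.0535)/0.0538 = 0.6%.
- The prognostic covariate was selected in 5.0% of runs, as step 1 predicts.

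The available gain depends on the assumed correlation r, roughly as 1 − √(1 − r²). This is 5% at r = 0.3, 13% at r = 0.5 and 29% at r = 0.7.

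**4. Different sets for different outcomes.** Ignoring clustering for simplicity, p < 0.05 needs a difference of 1.96 × √(2/n) SD. With the sample sizes in Table 5 this is 1.96 × √(2/150) = 0.23 SD for urine and 1.96 × √(2/1000) = 0.09 SD for diet. If tests are run within each analysis sample, a 0.2 SD imbalance would go unadjusted in the urine analysis, while half that imbalance would trigger adjustment in the diet analysis.

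**5. Whether covariates can reach β3 at all.** A covariate that does not change over time cancels out of each person's change. In a simulated example of Eq. 1 with complete pairs, adding a prognostic, imbalanced covariate as a main effect left β3 at 0.2494 and its SE at 0.0576, the same as without it. A second check gave the same invariance on complete cases after 20% loss (0.18856, SE 0.0479, both ways) and with one constant weight per person (0.20118, SE 0.0490, both ways). β3 moved only when people with a single visit were kept in (0.199 against 0.208).

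**The case against.** The strongest reply is that the rule touches only supplementary models. Eq. 1 is fixed in advance and carries the stratification factor. This stands, and it limits the importance of the point.

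A second reply is that under Eq. 1 with main effects on complete pairs, no choice of covariates changes β3 or its SE, so the rule can do no harm there. This also stands, but it helps the plan little: adjusted models of that form could not improve precision at all. It does mean that replacing the rule by a fixed list is not enough unless the way covariates enter is fixed too.

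A third reply is that selecting on imbalance adjusts exactly when a chance difference is largest. That is why the rule keeps about a quarter of the gain in the simulation. A fixed prognostic list corrects the same imbalances and keeps the rest.

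The missing threshold and candidate list may sit in an analysis plan that is not shown, and they are not held against the article. The rule itself is stated there.

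Three stronger readings are tempting, and the document does not support them:
- A reader might infer that selection inflates false positives or spoils coverage. The simulation showed 0.039 at a nominal 0.05, slightly conservative.
- A reader might infer room for a favourable choice of covariates. The Blinding section says that the analysts are masked, and selection uses baseline differences, not outcome effects.
- A reader might infer that village-patterned variables will be flagged far too often. That requires baseline tests that ignore villages, which the article does not say, and intra-cluster correlations well above the 0.02 it gives.

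**Conclusion.** The point holds for the additional adjusted models only. Choosing covariates by p-values between randomised arms selects on chance, picks a strong predictor about 5% of the time at 0.05, and gives up most of the precision sought: about a 3% cut in SD against about 13%, for one covariate with r = 0.5. It also makes the covariate set depend on the data and possibly differ by outcome.

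These sizes rest on an assumed threshold, correlation and number of candidates, and on a follow-up model without the baseline outcome. Once the baseline outcome is in the model, what further covariates add depends on what they explain beyond it, and the article gives no figure for that. The reasoning also assumes that allocation stays concealed from participants and data collectors through baseline, as planned. The main intention-to-treat analysis is unaffected and no type I error inflation is shown. The rule should be corrected, but it does not threaten the trial's main conclusion.

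**What to change.** Delete the sentence on p-value selection. In its place, name a short list of prognostic baseline covariates for each population from data already collected. Examples are age, education, wealth index and land cultivated for adults, and age and sex for children, together with district and the baseline outcome. The investigators should settle the list on subject-matter grounds before looking at the data by arm.

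State how the covariates enter, so that they reach the effect estimate. One route is a model for the 12-month outcome adjusted for its baseline value, with village clustering. The other is covariate-by-time terms in Eq. 1; the baseline outcome needs no extra term there because it is already a response. Main effects added to Eq. 1 on complete pairs would change nothing.

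Describe baseline balance with summary statistics and without significance tests. The cost is a change of wording and a little analysis work; no new data are needed.

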### Ethical oversight and study governance

The study protocol will be reviewed and approved by two ethics committees: (1) the Public Health Foundation of India’s Institutional Ethics Committee and (2) the University of Edinburgh’s Human Ethical Review Committee. Written informed consent will be obtained from all participants prior to conducting any assessments. The study is sponsored by the Academic & Clinical Central Office for Research & Development (ACCORD) at the University of Edinburgh, which provides oversight for clinical research conducted in the UK and oversees. The study is funded by the Medical Research Council/UK Research and Innovation and the Scottish Funding Council. The study sponsor and funders did not play a role in the study design and will not play a role in the collection, management, analysis, or interpretation of data; writing of the final report; or decision to submit the final report for publication.

The implementation of the BLOOM study will be overseen by a Study Management Committee (SMC), which meets at least monthly via video conference call. The study will also convene a Steering Committee with members who are independent from the study evaluation team. The Steering Committee will meet twice annually via video conference call. Their responsibilities, outlined in a Charter, will include: providing expert oversight of the study; monitoring recruitment rates; reviewing regular reports of the study from the SMC; assessing the impact and relevance of any accumulating external evidence; monitoring completion of CRFs; monitoring follow-up rates; commenting on any proposals by the SMC concerning any change to the design of the study, including additional ancillary studies; and overseeing the timely reporting of study results.

In addition to the SMC and Steering Committee, an Evaluation and Policy Advisory Committee (EPAC) will be formed with members from relevant state departments in Andhra Pradesh (health, agriculture, women and child development, education, and tribal welfare), the evaluation team, and the implementation team. The role of EPAC will primarily be to provide recommendations and connections to relevant initiatives and strategies at the state and national levels. They will also support dissemination of the research findings.

### Process evaluation

A three-part process evaluation will be conducted in accordance with Medical Research Council guidance for process evaluations of complex interventions [112]. First, implementation will be assessed including fidelity, dose, adaptations, and reach of the programme and how the programme was implemented (i.e., virtually versus face-to-face, group versus individual). Barriers and facilitators to implementation will also be assessed. Problems in implementation will be communicated to RySS as and when they appear.

Second, contextual factors that may influence the delivery of the programme or the study outcomes will be systematically recorded in all BLOOM villages. These factors will include other government programmes implemented in the village, any NGOs operating in the village and their activities, rainfall, and pest outbreaks. Third, mechanisms of impact including farmers’ adherence to the programme, acceptability of natural farming practices, and barriers and facilitators to adoption will be assessed.

Data will be collected using a combination of quantitative surveys, diaries, qualitative in-depth interviews with implementers and farmers, direct observations of trainings, and secondary data sources (e.g., routine government monitoring data on rainfall and pest outbreaks).

## Discussion

### Study implications

The BLOOM study will provide robust evidence of the impact of a large-scale transformational government-implemented agroecology programme on pesticide exposure and dietary diversity in agricultural households in rural Andhra Pradesh, India. It will also provide the first evidence of the health co-benefits of adopting agroecology, inclusive of malnourishment and common chronic diseases including type 2 diabetes and kidney disease, as well as early child development. In working closely with the government organisation responsible for implementation from the outset of the study, the study team will help to ensure that the study’s outcomes are priorities for the government and that the findings are rapidly disseminated and integrated into agriculture and public health policy in India. Whilst fully recognising that APCNF is unlikely to be the best solution in all contexts, this research study will provide evidence regarding its effectiveness in India with direct generalisation to other countries in South Asia and Africa considering adopting the approach [e.g., Nepal and Rwanda [113]].

This will be the first evaluation of a programme aimed at eliminating pesticide exposure among farmers in a low- or middle-income country to measure biomarkers of pesticide exposure. All previous studies in these contexts have relied on self-reported pesticide use. For example, our cross-sectional pilot study in Kurnool district, Andhra Pradesh, conducted between August and November 2020 found that APCNF farmers were 34% less likely to use synthetic pesticides compared to conventional farmers [12]. One cross-sectional comparison of n = 8 pesticide-free vegetable farmers and n = 11 conventional vegetable farmers in Chiang Mai, Thailand, found substantial reductions in urinary pesticide biomarkers [106].

Given that agroecology, including APCNF [114], explicitly promotes the diversification of crops cultivated, and crop diversity is positively associated with dietary diversity [114], one might expect agroecology to have an impact on dietary diversity. However, to the best of our knowledge, only one previous study, in Tanzania, has evaluated the impact of an agroecology programme on dietary diversity, finding significant improvements in child and women’s dietary diversity [30].

Thus, the BLOOM study will fill an important evidence gap relating to the human health co-benefits of sustainable agriculture. Given the wide breadth of outcomes evaluated in BLOOM, the study has the potential to inform the design of future programmes and interventions regardless of main outcomes of interest. Considering that agroecology is increasingly recognised as the way forward in agriculture interventions/programmes, this is especially relevant.

### Study strengths and limitations

The BLOOM study is led by a multi-disciplinary team of researchers and leverages a scientifically rigorous study design, employing cluster randomisation, which will strengthen causal inferences. The research questions were informed through discussions with policymakers and the government implementing agency, and government stakeholders have been involved since its inception. This is a randomised controlled evaluation in four districts of one state in south India and thus will not necessarily be generalizable to all districts in Andhra Pradesh nor all states in India. Nonetheless, these districts are relatively comparable to state- and national-level demographic and health characteristics (Table 2). The primary outcome of ∑DAPs will capture changes in organophosphate pesticides but not all pesticides. Our preliminary findings from Kurnool indicated that organophosphate pesticides were the most commonly reported pesticides used by farmers and the top-selling pesticides at retail shops [12]. However, if no change in ∑DAPs is observed, it will not be possible to make any conclusions about changes in other classes of pesticides such as pyrethroids, carbamates, neonicotinoids, or fungicides. Additional limitations include the use of self-report to assess dietary intake and APCNF fidelity.

